### Data collection and management

All research data will be documented on case report forms and the study diary. A pseudonymised identification number will be allocated to each participant. Study data will be transcribed from the source documents and stored electronically in a pseudonymised, password-secured database at Buchinger Wilhelmi Development und Holding GmbH. Documents allowing the identification of subjects (e.g., signed consent forms) will be stored securely and separately from the study data. Only representatives of the principal investigator, who are obliged to maintain confidentiality, have access to these data. The follow-up data will be collected using an online questionnaire that meets general data protection regulation standards. Data will always be treated confidentially and data protection regulations will be complied with. The source data will be kept for at least 10 years after the termination of the study.

### Statistical analysis

The statistical analysis of the data will be performed using R software for statistical computing. Given the longitudinal design of our study with multiple repeated measurements, a mixed model for repeated measures will be used for quantitative variables. The *p*-values from linear-mixed models in the longitudinal data analysis will be adjusted with a *post-hoc* Tukey test. Missing data will be handled with complete case analyses for the dependent variables or imputed using the median for auxiliary variables with less than 20% missing values. Subgroups will be generated using demographic data (e.g., sex) or unsupervised clustering methods. The statistical models will be adjusted for potential confounders such as age, gender, or baseline body weights. A parsimonious approach will be used. If a covariate does not influence the variance of the model, it will be excluded from the model. We will use multivariate statistics for metabolomics or metagenomics, including unsupervised (e.g., principal component analysis) and supervised statistical methods (orthogonal partial least squares discriminant analysis, sparse partial least square discriminant analysis). In the case of multivariate analyses (e.g., microbiome data), the false discovery rate corrected *p*-value (*q*-value of 5%).

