#### Body composition

The primary endpoints in this study are changes in whole body composition (fat mass, lean mass, and water) at the end of the fasting intervention as well as 1 and 4 months afterward compared to baseline measured by MRI (44–46) (Figure 3). Furthermore, changes in size and composition of heart (47–52), liver (53, 54), kidney, spleen, adipose tissue, lumbosacral muscle mass, and lower limbs (quadriceps, hamstrings, and calves) (55) over time as well as changes in brain morphometry (56, 57) will be assessed. Details of MRI measurements are provided as Supplementary material.

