### Sample size calculation

The required sample sizes vary between the outcome parameters. Previously, the effect size in matched subjects was 0.81 for T2 relaxometry in muscles (55). Using these assumptions, the minimal sample size requirement is 14 to detect meaningful acute changes in muscle physiology (alpha = 0.05, power = 0.80). MRS studies monitoring triglyceride (TG) content during CR (83, 84) observed that effect sizes were 1.09 and 0.59 in liver and muscle, respectively. Using the small effect size of muscle changes (alpha = 0.05, power = 0.80), the required sample size to detect organ-specific differences in MRS measurements is 28. To account for a potential drop-out rate of 15%, the sample size was set to 32.

Clinical routine laboratory examinations and other blood sample analyses will be performed on 100 samples. This number of participants was chosen to reach sufficient power for detecting differences in gut metagenome analysis. Large inter-individual differences are usually observed in the composition of fecal microbiomes. Small differences in alpha diversity (effect size 0.55) between two groups of 50 individuals can be detected with an 80% statistical power (85). Missing values are commonly encountered in fecal microbiome evaluations (85). Accounting for missing data and sufficient numbers to quantify bacteria abundance at the species level for at least 50 individuals, we estimated that 100 subjects are needed for this part of the study (power = 0.80). This is based on a fecal metagenome analysis, which included missing values for more than 50% of 612 bacterial species out of 724 species detected (86).

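### The 80% power for muscle triglyceride by MRS is computed at an unadjusted alpha of 0.05, but the Tukey-adjusted analysis over four visits would deliver about 63–67% with 27 evaluable participants

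*Protocol article*

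**What the plan says.** The Sample size calculation section of the protocol article gives three planning effects. For muscle T2 relaxometry, "the effect size in matched subjects was 0.81 for T2 relaxometry in muscles", from which it derives a requirement of 14. For triglyceride content by MRS, earlier calorie-restriction studies "observed that effect sizes were 1.09 and 0.59 in liver and muscle, respectively". The smaller of these two fixes the size: "Using the small effect size of muscle changes (alpha = 0.05, power = 0.80), the required sample size to detect organ-specific differences in MRS measurements is 28". Then: "To account for a potential drop-out rate of 15%, the sample size was set to 32". No allowance for multiple comparisons is mentioned.

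Study design gives four MRI/MRS time points for these 32 participants: before fasting, end of fasting, 1 month and 4 months. Under Body composition, the primary endpoints are changes at the three later times "compared to baseline measured by MRI".

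Statistical analysis specifies a mixed model for repeated measures, with p-values "from linear-mixed models in the longitudinal data analysis will be adjusted with a *post-hoc* Tukey test". It also specifies complete-case analysis for dependent variables. It does not list the comparisons that the Tukey adjustment covers.

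**The concern.** The test that was powered is not the test that will be run. The sample size rests on one paired comparison at 0.05. A Tukey adjustment over four visits conventionally covers six pairs and makes each comparison considerably stricter. Both elements are stated in the document, so this is a mismatch and not a detail left for a later analysis plan.

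The stake is the credibility of the 80% figure. A real change of the size assumed for muscle triglyceride would be missed more often than the one time in five that the protocol implies. Part of the loss comes from comparisons between later visits, which lie outside the baseline-referenced endpoint definition.

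**Working it through.** **Inputs.** From Sample size calculation: effect sizes 0.59, 0.81 and 1.09; alpha 0.05; power 0.80; required n 28; 32 enrolled; 15% dropout. From Study design: four visits. From Statistical analysis: Tukey adjustment. Assumptions: tests are two-sided; 0.59 is a mean change divided by the SD of the change; Tukey covers all pairs.

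**Evaluable number.** 32 × 0.85 = 27.2, so about 27.

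**Step 1: the plan's own figures.** For a paired t-test, power comes from the noncentral t distribution with n − 1 degrees of freedom and noncentrality d√n.

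- d = 0.81, n = 14: power 0.79986, which matches the stated 14 after rounding (strictly, 15 is the first n above 0.80).
- d = 0.59: n = 24 gives 0.790 and n = 25 gives 0.808, so 25 are needed against the stated 28. At n = 28, power is 0.853.
- Dropout: 28 / 0.85 = 32.9. The stated 32 agrees to within one participant.

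**Step 2: unadjusted power at the planned evaluable number.** d√n = 0.59 × √27 = 3.07, giving power 0.839. On its own terms the sizing is adequate.

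**Step 3: power under Tukey.** The critical value is c = q(0.95; k, df)/√2, where q is the studentized range quantile and k the number of visits. Power is the probability that a noncentral t with noncentrality 0.59√n exceeds c in absolute value. The residual df is bracketed between n − 1 and (k − 1)(n − 1).

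| Visits k | n | c | Alpha per comparison | Power |
|---|---|---|---|---|
| 4 | 27 | 2.743 to 2.625 | 0.0109 to 0.0104 | 0.628 to 0.670 |
| 4 | 28 | 2.737 to 2.623 | 0.0108 to 0.0104 | 0.650 to 0.690 |
| 4 | 32 | 2.714 to 2.616 | 0.0108 to 0.0104 | 0.729 to 0.763 |
| 3 | 27 | 2.485 to 2.413 | 0.0197 to 0.0194 | 0.717 to 0.741 |
| 3 | 32 | 2.461 to 2.401 | 0.0196 to 0.0194 | 0.804 to 0.823 |

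The rows with three visits are a sensitivity case: Table 2, as extracted, marks MRI and MRS at only three times. The table may be broken in extraction, and the text under Study design and Body composition supports four.

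With four visits, 80% power needs 35–37 evaluable participants (42–44 enrolled at 15% dropout).

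**Step 4: the other planning effects.** Tukey, four visits, n = 27:

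- d = 0.81 (noncentrality 4.21): power 0.92–0.94.
- d = 1.09 (noncentrality 5.66): power above 0.99.

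**Step 5: alternatives at d = 0.59, n = 27.**

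- Three baseline contrasts with a Dunnett-type adjustment (correlation 0.5 between contrasts; critical value 2.49 to 2.40): power 0.71–0.75 per contrast.
- Fixed sequence: the first contrast is tested at 0.05, with power 0.84.

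**The case against.** Several points on the other side stand.

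- **It is not the primary endpoint.** The 0.59 is for muscle triglyceride by MRS. Study design says the sub-cohort is powered for whole body composition, and a reader might infer that the primary endpoint has only 63–67% power. The document does not support that: it gives no effect size for fat mass, lean mass or water, so neither a shortfall nor adequate power can be shown.
- **The figure is conditional.** The Tukey family is not defined, and only the 0.81 is explicitly described as coming from matched subjects. Complete-case analysis within a mixed model may drop missing observations and not whole participants. More than 27 could then inform the end-of-fasting contrast, up to 73–76% power at 32. If there were only three visits and no dropout, 80% would be reached.
- **Tukey is valid.** It does not inflate type I error or bias any estimate, and not all of its extra pairs are wasted. The Aims section expects organs to re-expand after a transient decrease, and end of fasting versus follow-up tests exactly that.

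A reader might also conclude that 28 and 32 are arithmetic errors. The 32 is not: it lies within one participant of 28 / 0.85. The 28 exceeds the paired-t answer of 25, but the difference is conservative and no test is named. A Wilcoxon signed-rank basis would give 26 to 29.

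None of this removes the mismatch. The protocol sized the sub-cohort on 0.59 with a stated 15% loss, so that is the fair test of its 80% claim, and at 27 evaluable power falls below 80% with three visits or four.

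**Conclusion.** The concern holds for the effect on which the protocol itself sized the sub-cohort. Under an all-pairs Tukey adjustment over four visits, power for muscle triglyceride by MRS is about 63–67% with 27 evaluable participants and 73–76% with all 32, not 80%. The three-visit reading gives 72–74% and 80–82%. These figures assume two-sided tests and that 0.59 is a standardised paired difference. The shortfall does not extend to the two larger planning effects. The unexplained 28 is a minor reporting point and costs no power.

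**What to change.** 1. In Statistical analysis, replace the general Tukey statement for the imaging outcomes with the contrasts that the endpoint definition implies. Either test end of fasting versus baseline first at 0.05, followed in fixed sequence by 1 month and then 4 months versus baseline (power about 0.84 at 27 evaluable for the first contrast, at effect size 0.59), or apply a Dunnett-type adjustment to the three baseline contrasts (about 0.71–0.75).
2. Name the comparisons of end of fasting with 1 and 4 months as secondary, so that the re-expansion hypothesis keeps its test.
3. If Tukey is kept, state which pairs it covers and restate the power as about 63–67% at 27 evaluable.
4. In Sample size calculation, name the test behind 28: the paired t-test that matches 14 for 0.81 gives 25 for 0.59. Say also that the calculation concerns muscle triglyceride by MRS.

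The cost is wording only, with no extra participants. The Dunnett option still falls short of 80%. The fixed sequence restores it only for the first contrast, and a failure there stops formal testing of the later ones. Comparisons between later visits lose primary status.

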**FIGURE 1 F1:**
[figure not shown]
Main outcomes of the GENESIS study. By pooling knowledge acquired by macroscopic multi-organ fat distribution and composition provided by magnetic resonance imaging (MRI), with erythrocyte fatty acids, lipoprotein, peripheral blood mononuclear cell (PBMC) metabolome, protein persulfidation, and gut microbiome profiles, we aim to gain a deeper comprehension of molecular and physiological changes during fasting and food reintroduction.

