## Methods and analysis

### Aims

First, the GENESIS study aims to document changes in body composition and the contribution of the main metabolically active tissues (skeletal muscular tissues, adipose tissues, liver, heart, spleen, kidneys, and brain) to the metabolic switch during a 12-day fasting period. Changes in the size and mass of organs will be quantified. We hypothesize that a re-expansion and regeneration will follow a transient decrease of organ volume during fasting up to 4 months after food reintroduction. Protein resynthesis upon food reintroduction might correspond to an acceleration of the physiological protein turnover, which will be evaluated by measuring nitrogen excretion. Additionally, the organs’ specific compositions, especially the fat components, and their function will be documented along the fasting process. We hypothesize that these multi-system changes are safe, and that they could also be reflected by an improved cardiac and skeletal muscle metabolism and mitochondrial oxidative capacity which will be investigated by spiroergometry.

Second, the study focuses on fat storage, function, and exchange in adipose tissue, liver, spleen, kidney, and splanchnic tissue. Among the lipids studied, we focus on cholesterol metabolism during fasting, particularly sub-types of HDL, but also CEC and fatty acid profiles in the erythrocyte membrane.

Third, we will measure PBMC metabolome profiles to reveal cellular metabolic changes in circulating, easily accessible immune cells.

Fourth, we will determine whether persulfidation, which contributes to the maintenance of cellular oxidative functions, changes during fasting.

Last, we will measure if various metabolic and physiological changes, as described above, correlate to individual gut microbiota profiles. The composition and function of the fecal microbiota will be evaluated during LF using shotgun metagenomics. This will help us understand how intestinal microorganisms are linked to human physiology during fasting.

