#### Clinical data

Clinical data (e.g., body weight, body-mass-index, systolic and diastolic blood pressure, and heart frequency) will be documented at baseline, during fasting and food reintroduction as well as 1 and 4 months afterward. The abdominal circumference will be measured before and after fasting. Changes in ketonuria, capillary ketonemia, and capillary blood glucose levels will be measured during the fasting period and food reintroduction. Nitrogen balance, measured in 24-h urine samples (15), will be determined at baseline and during the fasting and food reintroduction period in the MRI subgroup only.

A clinical standard laboratory blood profile will be measured in each blood sample, during the transition day and after fasting (10). Additional blood samplings will be obtained from the first 32 subjects after three fasting days as well as 1 month afterward.

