#### Questionnaires

Several validated questionnaires will be recorded at baseline, at the end of fasting as well as 1 and 4 months afterward to document mental wellbeing (Warwick-Edinburgh Mental WellBeing Scale) (78), global health (PROMIS Scale) (79), physical activity (Godin Leisure-Time Exercise Questionnaire) (80), sleep quality (Pittsburgh Sleep Quality Index) (81), and dietary behavior (short healthy eating index survey) (82). Lifestyle habits like smoking behavior, alcohol consumption, or physical activity in hours/week will be self-reported. Participants will document energy level, emotional and physical wellbeing, as well as symptoms including fatigue, muscle weakness, back pain, hunger, anxiety, headache, and sleep disturbances on visual scales (0–10) at baseline, daily during fasting and food reintroduction as well as 1 and 4 months afterward.

Adverse events will be documented continuously.

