### Data analysis plan

The data of all clinical endpoints will be collected before and after 9 ± 3 fasting days. Demographic data and each participant’s medical history will be captured at baseline. The detailed timing of all measurements is shown in Table 2.

**TABLE 2 T2:** Summary of measurements.

	Before	Transition	Fasting days													Food reintroduction	+1 month	+4 months
Measurements	−5 to −2	−1	0	1	2	3	4	5	6	7	8	9	10	11	12			
Demographic data	x																	
Medical history	x																	
Anthropometric measurements	x	x	x	x	x	x	x	x	x	x	x	x	x	x	x	x	x	x
Vital signs	x	x	x	x	x	x	x	x	x	x	x	x	x	x	x	x	x	x
Blood sampling		x				x			x								x	
Capillary blood sampling	x	x	x	x	x	x	x	x	x	x	x	x	x	x	x	x		
First morning urine sampling			x			x			x								x	
24 h urine sampling	x		x	x	x	x	x	x	x	x	x	x	x	x				
MRI	x												x				x	
MRS P31 and H1	x												x				x	
Bioelectrical impedance analysis	x												x				x	
Quadriceps muscle ergometry	x												x				x	
Triaxial actigraphy	x		x	x	x	x	x	x	x	x	x	x	x	x			x	
Spiroergometry	x										x						x	
Stool sampling	x															x		
Visual scores: wellbeing, symptoms	x	x	x	x	x	x	x	x	x	x	x	x	x	x	x	x	x	x
Questionnaires and life style		x											x				x	x
Adverse events	x	x	x	x	x	x	x	x	x	x	x	x	x			x	x	x

Measurements only conducted in the first stage of this study (*n* = 32) are highlighted in blue.

Further, the Supplementary File contains a detailed description of the anthropometric data, vital signs, blood, urine and stool samples, the MRI and MRS acquisition protocols, bioelectrical impedance analysis, quadriceps muscle ergometry, triaxial actigraphy, and spiroergometry.

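### All-pairs Tukey adjustment wastes power on the daily secondary measures if visit is modelled as a factor: 29-31% against 51-53% for an assumed 0.3 SD change at n=100

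*Protocol article*

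**What the plan says.** The Statistical analysis section states that "a mixed model for repeated measures will be used for quantitative variables", and that p-values "from linear-mixed models in the longitudinal data analysis will be adjusted with a" post-hoc Tukey test. It neither exempts any variable nor lists contrasts.

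Several secondary measures are scheduled densely:
- Under Questionnaires, energy, wellbeing and symptoms are scored "on visual scales (0–10) at baseline, daily during fasting and food reintroduction as well as 1 and 4 months afterward".
- Under Clinical data, body weight and related measures, with "systolic and diastolic blood pressure, and heart frequency) will be documented at baseline, during fasting and food reintroduction", are recorded again at 1 and 4 months.
- Also under Clinical data, ketone measures and "capillary blood glucose levels will be measured during the fasting period and food reintroduction".

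Table 2 marks visual scores and vital signs in all 18 columns: before, transition, days 0 to 12, food reintroduction, +1 month and +4 months. Capillary blood is marked in 16.

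Two statements bear on which comparisons matter. The Body composition section defines the primary endpoints as changes from baseline. The Figure 1 legend adds recovery, with the aim of a "deeper comprehension of molecular and physiological changes during fasting and food reintroduction".

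The Data analysis plan also contains a sentence that points to a much simpler model: "The data of all clinical endpoints will be collected before and after 9 ± 3 fasting days".

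**The concern.** Tukey's procedure protects every pairwise comparison among the visits. With four visits that is six comparisons, and the price is modest. With 18 visits it is 153, of which only 17 compare a visit with baseline and a handful describe recovery. The rest, such as day 5 against day 9, mostly match no stated question but still raise the threshold for those that do.

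What is at stake is power on secondary measures such as fatigue, headache, sleep disturbance and blood pressure. A moderate change on a given day could be reported as non-significant when a smaller family, controlling the same error rate, would have detected it.

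**Working it through.** The document gives no power, alpha or effect size for the daily measures, so there is no planned figure to reproduce.

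**Inputs**
- Visits k = 18 for visual scores and vital signs (Table 2: 2 + 13 + 3). Treating each column as a level of time is an assumption.
- n = 100 (Study design). This is an upper bound, before dropout and shorter fasts.
- Family-wise alpha 0.05 within each measure. The value appears in the Sample size calculation section; two-sidedness is assumed.
- Effect d in SD of the within-person change. This is assumed, and a range is shown.
- Degrees of freedom from n-1 = 99 to (n-1)(k-1) = 99 x 17 = 1683. The ranges below reflect this.

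**Step 1: count the pairs.** 18 x 17 / 2 = 153. Against baseline: 17. Recovery (end of fasting against reintroduction, +1 month, +4 months): 3. The remainder is 153 - 17 - 3 = 133.

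**Step 2: Tukey threshold.** c = q(0.95; k, df)/sqrt(2) = 3.583 (df 99) to 3.494 (df 1683). The alpha per contrast, 2P(t > c), is 0.00053 to 0.00049.

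**Step 3: threshold for the smaller family.** The simultaneous multivariate-t critical value for the 20 contrasts was simulated under equal variances, with correlation 0.5 between baseline contrasts. It is 2.986 to 2.928, so alpha per contrast is 0.0036 to 0.0035.

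**Step 4: power.** Power = 1 - F(c; df, d x sqrt(n)), where F is the noncentral t distribution function. At d = 0.3 the noncentrality is 0.3 x 10 = 3.

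| Change on one day | Tukey, 153 pairs | 17 baseline + 3 recovery |
|---|---|---|
| 0.3 SD | 29-31% | 51-53% |
| 0.4 SD | 66-69% | 84-86% |
| 0.5 SD | 92-93% | 98% |

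The smallest change found with 80% power is 0.43-0.44 SD under Tukey and 0.38 SD under the smaller family.

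**Step 5: how far this depends on the assumptions (0.3 SD, n=100 unless stated)**
- Merging before and transition into one baseline (k = 17, 16 + 3 contrasts, df 99): 30% against 51%.
- Fasting data ending at day 6 (12 columns, 66 pairs): Tukey 37-39%, Dunnett against baseline only 58-60%.
- Four visits: 65-66% against 73-74% (Dunnett, baseline only).
- Two visits: 84% either way.
- Plain Bonferroni over the 20 contrasts (0.05/20 = 0.0025): 46-49%, so most of the gain does not need the Dunnett correlation structure.
- Serially correlated days (AR(1), 0.8 or 0.95): 54-57% for the smaller family.
- n = 80 (df 79): 19% against 38%.
- n = 32 (df 31): 3% against 10% at 0.3 SD and 20% against 40% at 0.5 SD. The marking of stage-1-only rows in Table 2 is not visible here. The Clinical data text limits only nitrogen balance and some extra blood samples to the first-stage participants, so 100 is the natural reading for the daily measures.

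**The case against.** **The model is not stated.** This is the strongest objection, and it stands as a condition. Table 2 is a measurement schedule, not a list of model terms, and the before-and-after sentence in the Data analysis plan would reduce clinical endpoints to two visits, with no loss. But the Tukey rule itself is stated without exception, and the section justifies its model by the repeated measurements, of which the daily rows are the densest.

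**The effect size is assumed.** This is also correct. The smallest effect used in the Sample size calculation section is 0.55, for microbial diversity. At 0.55 SD, Tukey has 97-98% power. The loss matters below about 0.5 SD.

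**Single-day power understates detection of a sustained change.** This is fair. If 0.3 SD is held over days 1 to 12, the chance that at least one fasting-day contrast with baseline is significant is 75-79% under Tukey, and an overall test of time would almost always detect the change (power above 99.9%). The smaller family still does better, at 92-93%.

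**Day-to-day pairs may be of interest**, for example onset and plateau of capillary glucose changes. This stands, and the fix allows for it.

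Two stronger readings are tempting. A reader might infer that the strict threshold lets harms pass as non-significant, because the Aims section says "We hypothesize that these multi-system changes are safe". The document does not support that. The statement follows organ composition and function, adverse events are documented separately and continuously, and nowhere is an adjusted p-value used to judge safety. A reader might also infer that the trial's main result is weakened. The primary MRI endpoints are measured at only a few visits, not daily, so this point does not reach them.

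**Conclusion.** The point holds as a conditional loss of efficiency. If the daily secondary measures are modelled with visit as an 18-level factor, the stated rule tests each baseline contrast at about 0.0005. At n=100 it then gives up about 22 percentage points of power at 0.3 SD (51 - 29) and 18 at 0.4 SD (84 - 66), compared with a family built around baseline and recovery. At 0.5 SD the loss is about 6 points (98 - 92).

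The family-wise error rate is controlled either way. The conclusion rests on day-by-day modelling, the assumed effect sizes, n=100 and a two-sided family-wise 0.05 within each measure. It is a worthwhile, low-cost improvement, not a defect that threatens the trial's conclusions.

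**What to change.** In the Statistical analysis section, for the measures recorded daily, replace all-pairs Tukey with a multivariate-t (Dunnett-type) adjustment from the same mixed model. The adjusted family for each measure would be:
- each visit against baseline;
- end of fasting against food reintroduction, +1 month and +4 months. For capillary blood, which Table 2 does not mark at the follow-up visits, only the first of these applies.

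If particular day-to-day contrasts matter, name them in advance and include them in the family. Analyses with few visits, including MRI, can stay as they are.

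The cost is two or three sentences, with no new data, visits or staff. The downside is that day-to-day pairs not named in advance are no longer formally tested.

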### Participants

Men and women aged 20–75 years with BMIs between 22 and 35 kg/m^2^ are eligible to participate if they match further eligibility criteria, as listed in Table 1. Any contraindication to fasting, as defined in the guidelines of fasting therapy including kidney, liver or cerebrovascular insufficiency (43) automatically leads to exclusion. Fulfilment of additional criteria related to contraindications for the MRI/MRS scans is required for participants of the MRI subgroup (Table 1).

**TABLE 1 T1:** Eligibility criteria.

Inclusion criteria	Exclusion criteria
• Men and women • Age between 20–75 years • BMI between 22–35 kg/m^2^ • Negative COVID-19 test • Available written declaration of consent	• Intake of medication (cardiovascular diseases, lipid, and glucose metabolism) • Chronic manifest psychical and psychiatric diseases • Participation in another study • Pregnancy or breastfeeding • Active uncontrolled gastrointestinal disorders including ulcerative colitis, Crohn’s disease, indeterminate colitis, severe irritable bowel syndrome, persistent infectious gastroenteritis, persistent or chronic diarrhea of unknown etiology, and recurrent *Clostridium difficile* infection • Major surgery of the gastrointestinal tract, in the past 5 years. Any major bowel resection at any time • Intake of antibiotics in the last 2 months • In the MRI subgroup, any MRI contraindication (claustrophobia, pacemakers, MR-incompatible prosthetic valves, metallic implants, and foreign metallic body)

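### Median fill for auxiliary variables is not confined to one-off baseline covariates; applied to a repeated measure, it can weaken change–microbiota correlations, from slightly to severely

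*Protocol article*

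**What the plan says.** The Statistical analysis section has two rules for missing data. For outcomes, "Missing data will be handled with complete case analyses for the dependent variables". For the rest, values are "imputed using the median for auxiliary variables with less than 20% missing values". The same section states that "a mixed model for repeated measures will be used for quantitative variables" and names age, gender and baseline body weight as examples of adjustment variables. It does not define *auxiliary*, and it does not say whether the median is that of the cohort, the time point or the participant.

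Two other sections bear on how far the rule reaches. Under Aims, the last aim reads: "we will measure if various metabolic and physiological changes, as described above, correlate to individual gut microbiota profiles". Table 2 schedules anthropometric measurements and vital signs before fasting, on the transition day, on each of days 0 to 12, during food reintroduction and at both follow-ups. Blood sampling is much sparser: the Clinical data section gives the day-3 and 1-month samples only to the first 32 participants.

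**The concern.** A single median is a tolerable stopgap for a covariate recorded once. It is a poor choice for one time point in a series, because the best information about the missing value is the same person's value on a neighbouring day. The median replaces that person's level with a typical person's level.

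If a change is then computed, it equals the median minus the person's own baseline, so people with high baselines appear to have large falls and people with low baselines appear to rise. Two things follow for the microbiota aim:

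- A real association between change and a microbial feature is diluted.
- A feature linked only to baseline level can appear linked to change.

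The filled values also enter the analysis as if they had been measured.

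**Working it through.** The document gives no imputation error, within-person correlation, SD of change or expected microbiota correlation, so there is no stated figure to reproduce. The check shows a range.

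**Inputs from the document**
- Missing share p below 20%, taken as 5%, 10% and 19%: "auxiliary variables with less than 20% missing values" (Statistical analysis).
- n = 100 for the microbiota part: "we estimated that 100 subjects are needed for this part of the study" (Sample size calculation).
- BMI limits 22 to 35: "Men and women aged 20–75 years with BMIs between 22 and 35 kg/m^2^ are eligible" (Participants).
- Alpha 0.05 (Sample size calculation), taken as two-sided.

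**Assumptions**
- Two time points with the follow-up value missing completely at random.
- The missing value is filled with that time point's cohort median, and a change is then derived.
- True change–microbiota correlation 0.40; within-person correlation ρ from 0.5 to 0.99.

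**Step 1: error in an affected change score.** With normal data, the mean distance of a value from the median is √(2/π) = 0.80 between-person SD. That is 3.2, 1.6, 0.8 or 0.4 times the mean change if the mean change is 0.25, 0.5, 1 or 2 SD. Only the filled records, under 20%, carry this error.

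**Step 2: share of the correlation retained.** With equal variances at both times,

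share = (1 − p/2)·√(2(1−ρ)) / √((1−p)·2(1−ρ) + p).

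Example, ρ = 0.9 and p = 0.19: 0.905 × 0.447 / √(0.81 × 0.2 + 0.19) = 0.405 / 0.593 = 0.68.

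| ρ | 5% missing | 10% missing | 19% missing |
|---|---|---|---|
| 0.5 | 97% | 95% | 91% |
| 0.8 | 94% | 89% | 80% |
| 0.9 | 89% | 80% | 68% |
| 0.95 | 81% | 69% | 55% |
| 0.98 | 66% | 52% | 38% |
| 0.99 | 52% | 39% | 28% |

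Simulated power at n = 100 and 5/10/19% missing is 0.96/0.91/0.77 at ρ = 0.9 and 0.77/0.56/0.35 at ρ = 0.98. Omitting the incomplete pairs keeps power at about 0.95–0.99 throughout. With Spearman correlation at ρ = 0.98, 92/85/71% is retained. If the change itself is filled with its own median, √(1−p) = 97/95/90% is retained.

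**Step 3: BMI as a very stable measure.** Assume baseline uniform on 22–35 (SD 13/√12 = 3.75), a mean change of −2 and a post-fast median of 26.5.
- The error in a filled change averages 13/4 = 3.25 kg/m², and 3.25/2 = 1.6 times the assumed change. Its maximum, at the eligibility limits, is 6.5.
- An SD of change of 0.4 or 0.8 implies ρ = 3.75/√(3.75² + SD²) = 0.994 or 0.978.
- The correlation of 0.40 falls to about 0.17/0.12/0.08 (SD 0.4) or 0.27/0.21/0.15 (SD 0.8) at 5/10/19% missing. Spearman gives about 0.26 at 19%.

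**Step 4: link to baseline.** In the BMI setting, the correlation of derived change with baseline is −p × 3.75 / SD of derived change. At p = 0.19 and SD of change 0.4, the SD of derived change is √(0.81 × 0.16 + 0.19 × 14.08) = 1.67, which gives about −0.43. Take a feature correlated 0.40 with baseline BMI but unrelated to change. Its simulated false-positive rate is about 12/20/40% at 5/10/19% missing instead of 5%. With SD of change 0.8 it is about 10/17/34%.

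**The case against.** The strongest reply is that the rule never reaches these data. The changes named in the microbiota aim are the study's outcomes. Read as dependent variables they are complete case, which is the very handling that keeps the correlation intact above. The adjustment variables named as examples are fixed or baseline values, for which a median fill does little harm. The plan specifies a mixed model and nowhere says that a change will be derived from a filled level. Anthropometrics are taken daily in a supervised clinic, so 19% missing post-fast weights may never occur.

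Much of this stands. A reader might infer that the plan makes change scores wrong by several times the real change and largely destroys the microbiota correlations. The document does not support that. It rests on one reading of *auxiliary* and of the median, on change scores the text does not describe, and on a within-person correlation of about 0.98 or more. Even in the BMI example the average error is 1.6 times the assumed change; larger multiples arise only towards the eligibility limits.

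What does not stand is that the matter is simply left to a fuller document. The article commits to a method and does not confine it to baseline covariates. In a model with a microbial feature as the outcome, physiological measures are explanatory, so the complete-case rule does not clearly cover them.

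**Conclusion.** The concern holds in a limited form. The median rule is stated without a restriction that it needs. Applied to a repeated measure, it discards the participant's own level, understates uncertainty, can attenuate change–microbiota correlations and ties the derived change to baseline.

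The harm runs from slight to severe. Retention is 68–97% at within-person correlations of 0.5–0.9. It drops below half at about 0.98 with missingness near the cap, or at 0.99 with about 10% or more missing. If the rule is meant only for baseline confounders, little is lost. These figures assume values missing completely at random, a time-point cohort median and a true correlation of 0.40. None of the three is given in the document.

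**What to change.** In the Statistical analysis section:

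- Define *auxiliary*, and limit median fill to one-off baseline covariates with few missing values.
- For time-varying auxiliary variables with nearby visits, such as daily anthropometrics and vital signs, use the participant's own adjacent values or the mixed model's individual prediction.
- Where no adjacent visits exist, use multiple imputation that includes baseline value, visit and sex, or omit the incomplete pair. This applies to blood variables in the 68 second-stage participants, who have no day-3 or 1-month sample, so interpolation is not possible for them.
- State that no change score will be derived from a median-filled level.

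This takes a few sentences and a few lines of R, and no new data. The only downside is slightly more programming.
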